**Methods:**

This non-randomised, two-arm pilot study will employ a pre-test/post-test parallel group design, comparing the exergaming intervention with a “routine treatment” control. Two high-secure, sub-acute wards in the Long Bay Hospital Mental Health Unit will be non-randomly allocated to either the exergaming intervention or the “routine treatment” control group.

The intervention group will receive a 12-week programme comprising three 30-min exergaming sessions per week using various Xbox Kinect^TM^ activity-based games designed to simulate moderate intensity exercise. The “routine treatment” group will continue to receive the standard model of care delivered by the Justice Health and Forensic Mental Health Network. Accelerometers will be distributed to all participants to collect daily energy expenditure, number of steps taken, intensity of physical activity and heart rate data throughout the study.

The primary outcomes are (1) intervention feasibility and acceptability, and (2) baseline to post-intervention changes in physical health outcomes (levels of physical activity; cardiovascular fitness; clinical measures of cardiometabolic risk). Secondary outcomes are baseline to post-intervention changes in mental health outcomes (depression, anxiety, stress, positive psychiatric symptoms). Outcomes will be assessed at baseline, mid-intervention, and post-intervention.

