### Study aims and objectives

This pilot study aims to investigate the feasibility, acceptability and potential effectiveness of a novel intervention (exergaming) to promote physical activity among patients of a secure mental health unit. The results will inform the design and methodology of a subsequent randomised controlled effectiveness trial.

The specific objectives of the study are to:Determine whether the pilot exergaming programme (FIT HEART) is a feasible intervention for improving physical activity levels among patients in a secure mental health unit, as measured by recruitment rates, retention in the programme, protocol adherence, and patient and staff acceptability ratings.Assess whether participants who receive the FIT HEART programme demonstrate greater improvements in physical activity levels and clinical physical health measures (anthropometry; blood parameters; blood pressure), compared to those who receive routine treatment only.

Based on the emerging evidence, it is hypothesised that the FIT HEART programme exergaming will be a feasible and acceptable form of physical activity intervention among this patient group. Findings on the potential effectiveness of the intervention as an adjunct to routine care in providing physical and mental health benefits to patients will inform hypotheses for a future randomised trial.

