#### Secondary outcomes

Baseline to post-intervention changes in mental health outcomes:Symptoms of depression, anxiety and stressPositive psychiatric symptoms

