##### Potential effectiveness of intervention

The potential effectiveness of the exergaming intervention will be assessed by measuring baseline to post-intervention changes in physical health outcomes:

i.Levels of physical activityii.Cardiorespiratory fitnessiii.Measures of cardiometabolic risk

**Physical activity: **Subjective levels of physical activity in the preceding week will be measured at baseline, mid-intervention and post-intervention using the Simple Physical Activity Questionnaire (SIMPAQ), a 5-item tool designed to assess physical activity and sedentary behaviour among people with mental illness [32]. The SIMPAQ measures self-reported activity over the previous week, including time spent in bed, sedentary time, structured exercise participation, and incidental or non-structured physical activity. In a validation study across 23 countries, the SIMPAQ was administered in a diverse sample of psychiatric patients, in both inpatient and outpatient settings, and found to be a reliable and valid tool for the assessment of self-reported physical activity [32].

Objective measures of daily physical activity during the study period will be obtained via accelerometry data. Following the baseline interview, all participants in both the intervention and comparison groups will be issued with an wrist-worn activity tracker (Fitbit® Charge 3) which they will be asked to wear the for the duration of the intervention period and up until the post-intervention assessments, totalling 14 weeks of activity monitoring. The Fitbits will only be worn whilst participants are out of their cell/room and participants will be required to check them in and out each day. Accelerometry data, obtained at 1-min intervals, will include number of steps taken, heart rate, energy (i.e. kilojoule) expenditure, and physical activity intensity as indicated by metabolic equivalent of task (METs) thresholds [33]. All participants will be provided with a weekly summary of their progress which will include their average steps over the preceding week, average heart rate, activity intensity levels (i.e. low, average, high) and average energy expenditure.

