#### Quantitative data

Quantitative feasibility outcomes will be reported descriptively and narratively. Rates of recruitment, retention, protocol adherence/compliance, intervention fidelity and adverse events will be presented as frequencies and proportions. Participants recruited to the study in the initial wave (January–March 2020), prior to the suspension of recruitment during the COVID-19 outbreak in NSW (March–June 2020), will be replaced by new participants to achieve the target sample size and will have their data excluded from the final analysis.

Primary and secondary outcomes will be analysed descriptively and presented for the overall sample and by group. Means, standard deviations and ranges, or medians and interquartile ranges, as appropriate, will be reported for continuous data, and frequency counts and proportions for categorical data, with associated 95% confidence intervals. Missing data for each of the primary and secondary outcome measures will be described using descriptive statistics. Missing data will not be replaced or imputed.

As this pilot study primarily aims to determine the feasibility of conducting a future definitive intervention trial and is not powered for statistical hypothesis testing, statistical analysis of the potential effectiveness of the intervention will not be performed on the clinical outcome data. Physical activity, cardiorespiratory fitness, and cardiometabolic risk data collected at each timepoint will be summarised descriptively for each group. Whilst between-group statistical comparisons will not be undertaken, post-intervention differences between groups will be reported using estimated mean differences and 95% confidence intervals, where appropriate.

Perceptions of exercise intensity, general health status and the study experience will be reported descriptively and narratively. All analyses will be performed using IBM SPSS software (Version 27) [40].

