### Strengths and limitations

A strength of the FIT HEART study is that it is the first to investigate the feasibility and acceptability of exergaming in a psychiatric inpatient setting and assess the potential impact of such an intervention on risk factors for cardiovascular and metabolic disease. Moreover, to our knowledge, it is the first study to trial an exergaming intervention in a correctional mental health facility.

This is a non-randomised and unblinded study and, as such, is potentially susceptible to bias and confounding, limiting the ability to draw causal inferences about the effectiveness of the intervention and generalisability of the findings to the target patient population. The study will be conducted in an inpatient setting, across two high-secure hospital wards, with patient placement according to level of acuity of psychiatric illness. Individual randomisation of participants to the control and intervention groups is not practical and will increase the risk of treatment contamination, as it will not be possible, within a particular ward, to ensure that participants in the control group avoid exposure to the intervention components. The use of a prospective design and a concurrent control group, however, will help to minimise selection bias associated with non-random allocation. Given the nature of the intervention, it is not feasible to blind participants and unit staff to the study conditions. By utilising objective measures of clinical outcomes (i.e. levels of physical activity, cardiovascular fitness, cardiometabolic risk), the risk of performance bias due to awareness of the intervention allocation will be reduced.

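### The one planned between-group estimate is a post-intervention difference, but objective 2 and the outcomes concern change from baseline, and the two wards are not randomly allocated

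*Protocol article*

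**What the plan says.** Under Study aims and objectives, objective 2 asks whether participants in the programme "demonstrate greater improvements in physical activity levels and clinical physical health measures" than those receiving routine treatment only. Under Potential effectiveness of intervention, effectiveness is to be judged by "baseline to post-intervention changes in physical health outcomes". The Secondary outcomes section uses the same form: "Baseline to post-intervention changes in mental health outcomes".

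The Quantitative data section sets out the analysis. For physical activity, fitness and cardiometabolic risk, "data collected at each timepoint will be summarised descriptively for each group". It then says: "Whilst between-group statistical comparisons will not be undertaken", "post-intervention differences between groups will be reported using estimated mean differences and 95% confidence intervals", with the qualifier that this is done where appropriate. No between-group difference in change and no baseline adjustment is mentioned. Missing data are not imputed.

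Under Study design, each arm is one ward, allocated according to the facilities available. Strengths and limitations describes the wards as operating "with patient placement according to level of acuity of psychiatric illness" and accepts that the study is open to bias and confounding.

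**The concern.** The stated target is a contrast in change between arms. The stated estimate is a contrast in end-of-study levels. Randomisation would give the two the same expectation, because baseline means would be equal on average. Here there is none, so any difference between the wards at entry is carried into the reported figure.

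A mean difference with a 95% interval will be read as an effect estimate even when no test accompanies it. The article says that the effectiveness findings will inform the hypotheses of a later randomised trial (Study aims and objectives) and that the study will inform its sample size and power (Sample size). An estimate that mixes a ward difference with a programme effect is a poor basis for either, and it uses less of the collected information than it could.

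**Working it through.** **Plan's own figure.** There is no power calculation to reproduce. The sample size is 30 per arm, 60 in total, with 20% attrition allowed for. If 30 are enrolled, 30 × 0.8 = 24 per arm are evaluable.

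**Assumptions not in the documents.** Baseline-to-post correlation ρ from 0.3 to 0.9; baseline ward gap d from 0.2 to 0.5 SD; equal SD at both timepoints; independent participants within wards.

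**What the planned figure estimates.** By identity:

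post difference = baseline difference + difference in change.

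The planned figure therefore matches the target only if the baseline difference is zero.

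**Effect of a stable gap with no programme effect.** Simulation, 24 per arm, 20,000 replicates for each setting, ρ = 0.5, 0.7 and 0.9:

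| Gap d (SD) | Bias, post-only | Post-only CI excludes 0 | Bias, difference in change | Change CI excludes 0 | ANCOVA bias (1−ρ)d at ρ = 0.5 / 0.7 / 0.9 |
|---|---|---|---|---|---|
| 0.2 | 0.20 | about 10% | about 0 | about 5% | 0.10 / 0.06 / 0.02 |
| 0.3 | 0.30 | about 18% | about 0 | about 5% | 0.15 / 0.09 / 0.03 |
| 0.5 | 0.50 | about 40% | about 0 | about 5% | 0.25 / 0.15 / 0.05 |

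The last column is from the formula, not simulated.

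If the gap instead shrinks to ρd by the end of the study, the post-only difference is biased by ρd, ANCOVA is unbiased, and the difference in change is biased by −(1−ρ)d. For example, at d = 0.3 and ρ = 0.9 the post-only bias is 0.27 SD rather than 0.30 SD. The data cannot say which pattern holds, which is a reason to show both baseline-using estimates.

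**Precision.** 95% half-widths in SD units, n = 24 per arm:

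- Post-only: t(0.975, 46) × √(2/n) = 0.581, whatever ρ is.
- Difference in change: t(0.975, 46) × √(2(1−ρ) × 2/n).
- ANCOVA: t(0.975, 45) × √((1−ρ²) × 2/n).

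| ρ | Post-only | Change | ANCOVA | ANCOVA narrower than post-only by |
|---|---|---|---|---|
| 0.3 | 0.58 | 0.69 | 0.56 | about 5% |
| 0.5 | 0.58 | 0.58 | 0.50 | about 13% |
| 0.7 | 0.58 | 0.45 | 0.42 | about 29% |
| 0.9 | 0.58 | 0.26 | 0.25 | about 56% |

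With all 30 per arm evaluable, the post-only half-width is 0.52 SD and the ANCOVA half-widths are 0.49, 0.45, 0.37 and 0.23 SD.

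The ANCOVA formula takes the observed baseline difference as negligible. An observed gap of 0.5 SD multiplies the half-width by about √(1 + (0.25/46)/(2/24)) = 1.03, so at ρ = 0.3 the gain all but disappears (0.555 × 1.03 = 0.57). The change score alone is less precise than post-only when ρ is below 0.5.

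**Which outcomes have a baseline.** Under Data collection and in Table 1, the SIMPAQ, step test, anthropometry, blood pressure, blood measures, DASS-21 and CAPE-P15 are all taken at baseline. The activity tracker is issued only after the baseline interview, so no pre-intervention tracker value is described.

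**The case against.** Five points can be made for the plan.

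- **Baseline is not ignored.** Each timepoint is summarised by group, so a ward gap would be visible. Since the outcomes are defined as changes and are to be presented by group, within-group change may already be intended. This stands: a reader who infers that the baseline data go unused goes too far. It does not supply the missing contrast. Subtracting group means gives a point estimate but no interval without the within-person correlation, and with no imputation the baseline and post means may come from different participants.
- **The SAP may add adjustment.** The article defers detail to a later SAP, and an estimated mean difference does not exclude a covariate. That is fair as to the estimator. The article nevertheless fixes the contrast as post-intervention, so this is a stated choice and not an omitted detail.
- **No imbalance is shown.** Both wards are sub-acute, male, 15-bed units of one hospital, and the remark on acuity explains why individual randomisation was impractical. This stands. A reader might infer that baseline differences in weight, fitness or glucose are to be expected; the documents support only a risk.
- **The contrast decides nothing.** No test is planned, and the progression criteria in Table 2 cover recruitment, retention, adherence and fidelity. This stands and limits the severity.
- **Adjustment is no cure.** ANCOVA leaves (1−ρ)d under a stable gap, and with one ward per arm no baseline adjustment separates ward from programme. This also stands, and the fix has to say so.

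**Conclusion.** The mismatch is real. The only between-group estimate in the plan is a difference in post-intervention level, while objective 2 and the outcomes concern change. In two non-randomly allocated wards the two coincide only if baseline means are equal.

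Under the assumed gaps of 0.2 to 0.5 SD, the post-only interval would exclude zero in about 10% to 40% of null trials. It is also wider than the baseline-adjusted interval, slightly at ρ = 0.3 and by more than half at ρ = 0.9. The documents give neither a ward gap nor a correlation, so these are ranges and not predictions.

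It would be tempting to conclude that the interval is far too wide in general, or that the decision to proceed is compromised. The first holds only for high correlations. The second is not supported, because no progression criterion uses this contrast. Severity is moderate: the consequence falls on what the pilot passes to the planning of the randomised trial.

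**What to change.** Replace the sentence on post-intervention differences in the Quantitative data section, or settle it in the SAP before analysis, along these lines:

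*For each continuous outcome with a baseline measurement (SIMPAQ, step test, anthropometry, blood pressure, blood measures, DASS-21, CAPE-P15), we will report, in participants with both measurements, the between-group difference in mean change from baseline and the baseline-adjusted mean difference (ANCOVA of the post value on group and baseline value), each with a 95% CI, beside each group's mean change. These are estimates only; no p-values will be given.*

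Add two statements of limits: if a ward gap is stable over time, ANCOVA leaves (1−ρ) times that gap; and with one ward per arm neither estimate removes ward-level confounding. State also that activity-tracker data are outside this rule because no pre-intervention value is described, and label any group difference in them as unadjusted for baseline.

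The cost is a few sentences. The baseline measurements are already scheduled, no participants or visits are added, and the decision not to test hypotheses is unchanged.

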#### Qualitative data

Qualitative data on intervention acceptability obtained from the patient and staff evaluation surveys administered post-intervention will undergo thematic analysis, using both deductive and inductive coding methods [41], and iterative categorisation (IC). IC entails an iterative process of constant comparison between the data and emerging thematic categories [42]. This mixed-method approach to coding will entail using a priori codes derived from the evaluation surveys.

### Progression criteria

The decision to proceed to a definitive RCT will be informed by an assessment of feasibility outcomes according to a set of progression criteria determined a priori by the project team (Table 2). These criteria were developed utilising the traffic light system, as proposed by Avery et al. [43]. Green (go) indicates that the criteria have been met and that progression to the RCT is possible without changes to the design or implementation of the intervention, amber (amend) indicates that some changes should be made to the protocol, and red (stop) indicates that the RCT should not proceed.

**Table 2 Tab2:** FIT HEART progression criteria

	Green	Amber	Red
Recruitment			
% of eligible patients consenting to participation	≥ 50%	30–49%	< 30%
Retention			
% of recruited participants retained at post-intervention data collection timepoint with valid primary outcome data	≥ 80%	70−79%	< 70%
Protocol adherence			
% of recruited participants who adhere to allocated intervention	≥ 70%	50–69%	< 50%
% of recruited participants who comply with wearing an accelerometer	≥ 90%	70–89%	< 70%
Fidelity of intervention delivery			
% of intervention components delivered as per protocol	≥ 90%	70–89%	< 70%

### Oversight and monitoring

Coordination and oversight of the trial will be provided by the JHFMHN Research Unit (Investigators [name]). Data management will be overseen by [name].

#### Safety monitoring and reporting

Safety monitoring and reporting procedures will be aligned with the requirements for clinical trials conducted in Australia [44] and in NSW Public Health Organisations in particular (*Office for Health and Medical Research Policy Directive PD2017_039-Safety Monitoring and Reporting for Clinical Trials Conducted in NSW Public Health Organisations*).

The occurrence of any unexpected or adverse events during the study period, irrespective of whether they may be causally related to the study, will be recorded. Daily monitoring of adverse events will be conducted via brief interviews with staff and patients and health record review. An adverse event that meets the criteria for a serious adverse event (SAE) will be reported to all relevant ethics committees: JHFMHN Human Research Ethics Committee (HREC), Aboriginal Health & Medical Research Council (AH&MRC). SAEs occurring after a subject has withdrawn from, or completed participation in, the study will not be reported unless the investigators believe that the event may have been caused by the study intervention or a protocol procedure. Investigators will determine potential causality based on whether there is a temporal relationship to participation in the study, as well as whether the event is unexpected or unexplained given the participant’s previous medical conditions and current medications.

Prior to each exergaming session, the Dynamic Appraisal of Situational Aggression (DASA) will be completed for each participant. The DASA is an instrument designed to assess the risk of imminent violence (i.e. within 24 h of administration) in psychiatric patient populations [45]. Any participant that presents a risk of aggression/violence will be excluded from the session for that day and will recommence sessions subject to re-appraisal of risk.

In cases where a participant discloses, or research staff are alerted to, a new and/or unmanaged health condition during the course of the study, a referral form will be completed and handed over to clinical staff at the study site for appropriate follow-up. Information alerting participants to this referral process is included in the PIS.

## Discussion

The patient and environmental factors of secure mental health units present unique challenges to the integration of conventional physical activity interventions into routine care. This protocol describes the design and methods of a non-randomised, two-arm pilot study assessing the feasibility, acceptability and potential effectiveness of implementing a novel exergaming-based intervention (FIT HEART) among patients of a secure mental health unit. Participants in the intervention group will receive a 12-week programme, comprised of three 30-min exergaming sessions per week, with those in the control group receiving routine care. The primary objective of the study is to determine whether the FIT HEART programme is a feasible intervention for improving physical activity levels, as measured by recruitment rates, retention in the programme, protocol adherence, and patient and staff acceptability ratings. Baseline to post-intervention changes in physical health outcomes (levels of physical activity; cardiovascular fitness; clinical measures of cardiometabolic risk) will also be assessed. The results will be disseminated in peer-reviewed journals and at national and international conferences and, if suggestive of intervention feasibility and acceptability, will inform a larger RCT of effectiveness, in which multiple follow-up points will be used.

### Strengths and limitations

A strength of the FIT HEART study is that it is the first to investigate the feasibility and acceptability of exergaming in a psychiatric inpatient setting and assess the potential impact of such an intervention on risk factors for cardiovascular and metabolic disease. Moreover, to our knowledge, it is the first study to trial an exergaming intervention in a correctional mental health facility.

This is a non-randomised and unblinded study and, as such, is potentially susceptible to bias and confounding, limiting the ability to draw causal inferences about the effectiveness of the intervention and generalisability of the findings to the target patient population. The study will be conducted in an inpatient setting, across two high-secure hospital wards, with patient placement according to level of acuity of psychiatric illness. Individual randomisation of participants to the control and intervention groups is not practical and will increase the risk of treatment contamination, as it will not be possible, within a particular ward, to ensure that participants in the control group avoid exposure to the intervention components. The use of a prospective design and a concurrent control group, however, will help to minimise selection bias associated with non-random allocation. Given the nature of the intervention, it is not feasible to blind participants and unit staff to the study conditions. By utilising objective measures of clinical outcomes (i.e. levels of physical activity, cardiovascular fitness, cardiometabolic risk), the risk of performance bias due to awareness of the intervention allocation will be reduced.

Impediments to recruitment and retention may impact on the sample representativeness and power to detect the primary outcomes of interest. In planning the recruitment strategy, bed capacity in each of the units, patient length of stay, and participant attrition has been considered. Nevertheless, attainment of the desired sample size is subject to patient flow through the unit and willingness to participate in the study. Recruitment may also be impacted by intermittent restriction of access to units and participants during periods when the unit is in lockdown due to staffing or security issues. A potential challenge for the study will be retaining participants for the duration of the 14-week assessment period due to unforeseen release or transfer from the Long Bay Mental Health Unit. In cases of release or transfer prior to week 12 of the study period, all efforts will be made to complete the “early discontinuation” assessments prior to discharge or in the week following transfer to another JHFMHN health centre.

The primary aim of the study is to determine the feasibility and acceptability of implementing the FIT HEART programme as an adjunct to routine care. Notwithstanding potential limitations and challenges, piloting the intervention in a real-world patient setting will contribute to an emerging evidence base and provide important information ahead of a more rigorous randomised controlled trial.

